#### Clinical data

Demographic and medical information is retrieved from an open interview with both patient and informal caregiver and physical examination by a clinician.

The Mini Mental State Examination is used to detect cognitive impairment, to assess its severity and to monitor cognitive changes over time [14]. The Clinical Dementia Rating scale (CDR) [15,16] provides a global rating of dementia severity. The Geriatric Depression Scale-15 [17] is applied to detect depression. Patient’s behavioural and psychological problems are measured by the Neuropsychiatric Inventory (NPI) [18]. The Disability assessment for Dementia (DAD) is assessed to evaluate basic and instrumental activities in daily activities [19]. The information of both the NPI and DAD is obtained from a caregiver familiar with the patient’s behaviour by means of a semi structured interview. Caregiver’s burden of care is assessed using the disease specific Sense of Competence Questionnaire (SoCQ) [20,21].

Neuroimaging markers include medial temporal lobe atrophy measurements and white matter lesions which are qualitatively scored based on 3 T MRI scan images.

Neuropsychological examination consists of a standardized battery of cognitive tests performed by a (neuro)psychologist. Tests include Rey’s Verbal Learning Test [22,23], Visual Association Test [24], and Digit-Span [25] to assess memory; Letter Digit Substitution Test [26] to assess mental processing rate; and Stroop Color-Word Test [27] and Trail Making Test [28,29] to assess attention, concentration and interference. Raw scores were converted to z-scores, adjusting for age, education and gender.

#### Quality of life data

Patient’s generic quality of life is measured by the EQ-5D instrument. It was developed and validated in a number of European countries including the Netherlands [30-32] and it has been validated in patients with dementia [33,34]. The EQ-5D describes health status according to five three-level dimensions, which yields 243 potential combinations of health states. Each combination leads to a utility score by means of an additive function derived from the UK general population [35,36].

Patient disease specific quality of life is measured by the validated Quality of Life – Alzheimer’s Disease scale (QoL–AD) [37,38]. It has 13 items covering the domains of physical health, energy, mood, living situation, memory, family, marriage, friends, self as a whole, ability to do chores around the house, ability to do things for fun, money, and life as a whole. Scale scores range from 13 to 52 with higher scores indicating greater QoL. An improvement of 3 points on the QoL-AD is judged as clinically relevant as this indicates a change of well-being on one of the domains from very poor to excellent [39].

Patient EQ-5D is assessed by the patient during the visit to the memory clinic. Furthermore, the informal caregiver judges the EQ-5D and QoL-AD for the situation of the patient and for his/her own situation and fills this out in the booklet of questionnaires.

Care-related quality of life of informal caregivers is assessed by the CarerQol[40]. It combines seven important burden dimensions with a valuation component (a visual analogue scale (VAS)) for happiness. The seven burden dimensions are 1) fulfilment; 2) relational problems; 3) mental problems; 4) problems with daily activities; 5) financial problems; 6) support; and 7) physical problems. The CarerQol-VAS ranges from 0 (“completely unhappy”) to 100 (“completely happy”) and has been validated in a Dutch sample of heterogeneous caregivers.

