## Methods/design

### Study design

A cohort design was chosen because an assessment of test combinations within a randomized controlled trial would require the evaluation of many diagnostic strategies for which the number of subjects needed would exponentially increase [13]. To determine the diagnostic value of emerging biomarkers for AD and related disorders both a clinical diagnosis and diagnosis based on emerging biomarkers (index tests) are compared with a reference diagnosis. Due to limited ability of biopsy (which is unethical) or autopsy (which requires follow up until death) a two-year follow up of the clinical course is used as a proxy to obtain information on the state of the disease at baseline; so-called delayed-type cross-sectional accuracy study design [12]. Four academic memory clinics (Leiden University Medical Centre, Maastricht University Medical Centre, Radboud University Nijmegen Medical Centre and VU University Medical Centre) specialized in the diagnosis and treatment of memory disorders participate in the study. Two memory clinics are settled within a department of geriatrics, one within neurology and one within psychiatry. The study is performed within the framework of CTMM, the Center for Translational Molecular Medicine (http://www.ctmm.nl), a Dutch public-private partnership; project LeARN (grant 02 N-101).

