#### Research goal 3: Decision analytic model

Finally a decision analytic model is built which provides a framework combining available evidence from different resources among which (accuracy) results from the study, literature and expert opinion. A decision analytic model can be defined as a set of mathematical relationships that form a structure reflecting the natural progression of a disease. By simulating patients or fractions of a population, these models enable the estimation of the likelihood of each consequence and its corresponding costs and effects [48]. It is applied to evaluate the short-term cost-effectiveness in terms of cost per correct diagnosis and long-term cost-utility in terms of cost per quality adjusted life year gained of diagnostic strategies under evaluation. Utility scores will be used to calculate Quality Adjusted Life Years (QALY). Patients who pass away during the year covered by the evaluation will be given a utility score of zero from the exact time of death. QALYs will be derived using the trapezium rule. A societal viewpoint will be adopted including the evaluation of all relevant costs and effects to calculate the societal benefits.

The cohort design facilitates the evaluation of many different diagnostic procedures by varying the place of a new diagnostic marker in the clinical pathway. Each procedure generates specific proportions of correct or incorrect diagnoses. Average costs and effects of correct and incorrect diagnoses are applied to calculate the total costs and effects of each procedure.

Sensitivity analysis will be performed taking into account both first order uncertainty regarding variation between patients in a homogeneous group and second order uncertainty regarding the true value of the parameters included in the model. This also enables the evaluation of an earlier diagnosis, different test sequences and the effect of possible new disease modifying drug treatments.

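### EQ-5D utilities are scored with UK public preferences in a Dutch study with a societal viewpoint, without a stated reason or a sensitivity analysis on the value set

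*Protocol article*

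**What the plan says.** Four places in the Protocol article bear on this point.

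- **Scoring (Quality of life data).** The instrument is the three-level version: "The EQ-5D describes health status according to five three-level dimensions, which yields 243 potential combinations of health states". The step from health state to utility is then fixed: "Each combination leads to a utility score by means of an additive function derived from the UK general population". The Netherlands is mentioned just before, but about the questionnaire and not the weights: "It was developed and validated in a number of European countries including the Netherlands".
- **Use of the utilities (Research goal 3: Decision analytic model).** The utility scores are turned into QALYs by the trapezium rule. They serve to estimate "long-term cost-utility in terms of cost per quality adjusted life year gained of diagnostic strategies under evaluation".
- **Perspective (same section).** "A societal viewpoint will be adopted including the evaluation of all relevant costs and effects to calculate the societal benefits".
- **Setting (Study design; Cost data).** The study runs in "Four academic memory clinics (Leiden University Medical Centre, Maastricht University Medical Centre, Radboud University Nijmegen Medical Centre and VU University Medical Centre"), within "a Dutch public-private partnership". Resource use, caregiver time, productivity losses and out-of-pocket spending are collected from these patients and their caregivers by questionnaire booklet.

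The sensitivity analysis in the Research goal 3 section covers variation between patients and uncertainty about parameter values. It also names earlier diagnosis, test sequence and possible disease-modifying treatment. It does not mention the value set.

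**The concern.** A utility combines two things: the health state that a respondent reports, and the weight that some public attaches to that state. Here the reports come from Dutch patients and caregivers and the weights from the UK public. Under a societal viewpoint that covers effects as well as costs, the natural base case weights health by the preferences of the society studied. The plan departs from this without saying why.

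What is at stake is the QALY denominator of the long-term result under research goal 3. If the two publics weight health states differently, the cost per QALY reported for a biomarker strategy would differ under Dutch weights. A reader of that result would not know by how much, because no alternative scoring is planned. A decision maker could also take the QALYs to carry Dutch preferences when they do not.

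**Working it through.** **1. The plan's own figure.** Five dimensions with three levels each give 3^5 = 243 health states, which matches the stated 243. The instrument is described consistently. The point concerns only the weights attached to those states.

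**2. Where the value set enters.** An additive function can be written as

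u(state) = a + b1(level on dimension 1) + ... + b5(level on dimension 5).

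The respondent supplies the levels. The value set supplies a and the b terms. Changing the value set changes a and b and leaves every collected answer as it is.

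**3. From utilities to QALYs.** The Data assessment section has the caregiver booklet filled out at baseline and at 3, 12 and 24 months. The intervals are 0.25, 0.75 and 1.00 years. The trapezium rule gives

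QALY = 0.25(u0 + u3)/2 + 0.75(u3 + u12)/2 + 1.00(u12 + u24)/2
= 0.125 u0 + 0.5 u3 + 0.875 u12 + 0.5 u24.

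The coefficients sum to 0.125 + 0.5 + 0.875 + 0.5 = 2.0 years, as they should. For the patient's own ratings at the clinic visits (baseline, 12 and 24 months) the rule gives 0.5 u0 + 1.0 u12 + 0.5 u24, which also sums to 2.0. Every term is scored with the chosen weights, so the choice affects the whole QALY whichever respondent is used.

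**4. From QALYs to the result.** Cost per QALY gained = (difference in cost) / (difference in QALYs). The value set affects only the denominator.

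**5. Can the size be computed?** That would need the UK weights, a second set of weights, the distribution of health states, and the differences in QALYs and costs between strategies. The document gives none of these.

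A single multiplier is no substitute. If every QALY difference were multiplied by the same k, cost per QALY would be multiplied by 1/k. But two additive functions need not differ by one common factor across 243 states. Consider also a second function that adds a constant c to every living state. Differences between living patients are unchanged, because c cancels. Survival time gained is now worth u + c per year in place of u, because the plan sets utility at zero from death. The same change of weights can thus leave one part of a QALY gain alone and shift another. Neither a percentage nor a direction can be supported.

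**6. Does the planned sensitivity analysis cover it?** Parameter uncertainty varies estimates around values already scored with the UK function. It does not replace that function, and none of the scenarios named does so either.

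**7. What is not touched.** Sensitivity, specificity, the other accuracy measures and cost per correctly diagnosed patient contain no utility term. The effect is confined to utility-based results.

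**The case against.** The strongest reply is that the plan does not contradict itself. A reader might infer that a societal viewpoint combined with UK weights is an internal contradiction. The text does not support that. It defines the viewpoint by scope, namely which costs and effects count, and never says whose preferences must weight the health states. This part of the objection stands.

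The Dutch target is also inferred. The Background section speaks of decision makers without naming a country, and the model draws on literature and expert opinion as well as on study data. No country is given for unit prices. It would therefore go too far to say that costs and effects belong wholly to two different societies: the health states are Dutch too, and only the weights are known to be from the UK.

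A reader might further infer that the weights matter most in moderate and severe states, and that those states separate correctly from incorrectly diagnosed patients. Nothing in the document shows either. Entry is limited to a Mini-Mental State Examination score of at least 20 and a Clinical Dementia Rating of 0 to 1.

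It can also be said that a condensed article leaves rationale and alternative scenarios to a fuller document. That carries less weight here, because the article states the value set explicitly. The Dutch validation it mentions concerns the questionnaire, and international comparability, a possible reason for UK weights, is not claimed. The fact that answers can be re-scored later shows that the remedy is easy. It does not justify the base case.

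**Conclusion.** The point holds as a stated choice that can be improved at little cost. The plan scores EQ-5D with UK general-population weights, applies them to health states reported in Dutch clinics under a societal viewpoint, gives no reason, and names no alternative scoring. Cost per QALY would then value health by the preferences of a different public from the one studied.

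The size is unknown and may be small, and the direction is unknown. The reach is limited to the cost-utility part of research goal 3, which the plan itself describes as a preliminary model.

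The conclusion rests on two assumptions: that the Dutch setting indicates the society whose viewpoint is meant, and that a Dutch value set for the three-level EQ-5D is available to the sponsor. If the first fails, the plan should still say whose preferences the QALYs represent. If the second fails, that statement is the whole remedy.

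**What to change.** Score the base case with a Dutch general-population value set for the three-level EQ-5D, assuming one is available, and report the UK function as a named sensitivity analysis. Apply the same rule to patient and caregiver ratings. If UK weights stay in the base case, give the reason, state next to the cost-per-QALY result that the QALYs reflect UK preferences, and add the Dutch scoring as the sensitivity analysis where it is available.

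The cost is a re-scoring of answers collected in any case and one extra model analysis. No new data, patients or visits are needed. The downside is slightly less direct comparability of the base case with UK-scored studies, which the UK sensitivity analysis largely restores.

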#### Cost data

Cost data are retrieved by the composed booklet of questionnaires. Patient resource utilization and caregiver time, which often contains productivity losses, are assessed by means of the short version of the Resource Utilization in Dementia-questionnaire (RUD-lite). This instrument has been validated and proved to register over 95% of the costs involved in AD-care [41]. Work status, income, and productivity losses of both the patient and caregiver are assessed by the adjusted PRODISQ (PROductivity and DISease Questionnaire) [42]. The consequences of informal caregiving on paid or unpaid work are assessed by the Health and Labour Questionnaire on a two-week scale on which is indicated whether one was ill, ill by caregiving or not ill [43]. Additional questions are asked referring to the number of visits to various health care professionals, resources or aids that are bought and other out-of-pocket costs.

#### Emerging biomarker data

Biomarkers can be divided into two categories, one reflecting the presence of beta-amyloid protein (Aβ) and one reflecting neuronal degeneration or injury. A pathological cascade is hypothesized in which basically Aβ markers become abnormal first, followed by neuronal injury [9,44].

The biomarkers included in this project are outlined in Table 3. CSF is collected and Amyloid β42, total tau and phosphorylated-tau are analyzed using a standardized quantitative method. FDG uptake and Pittsburgh compound B binding (PiB) on PET are both qualitatively rated by a radiologist and quantitatively analyzed by standardized methods. Whole brain and hippocampal volume, white matter integrity and functional connectivity derived by MR imaging are quantitatively analyzed by a researcher. These tests are not part of the current routine clinical diagnostic procedure. They are judged and analyzed independently and blindly. The outcome of each test is dichotomous or continuous, both for AD aetiology and progression of cognitive decline.

**Table 3 T3:** Included biomarkers in the project categorized by reflecting Aβ or neuronal injury

**Technique**	**Aβ accumulation**	**Neuronal dysfunction**
CSF	Amyloid β42 in the CSF	total tau and phosphorylated-tau in CSF
PET	amyloid tracer uptake in PET	fluorodeoxyglucose PET
MRI		White matter integrity (DTI)
		Functional connectivity (rsfMRI)
		Whole brain volume
		Hippocampal volume

Abbreviations: Aβ, beta-amyloid protein; CSF, cerebrospinal fluid; DTI, diffusion tensor imaging; MRI, magnetic resonance imaging; PET, positron emission tomography; rsfMRI, resting state functional magnetic resonance imaging.

### Baseline clinical diagnosis and reference diagnosis

Current clinical practice diagnosis is reflected by a consensus procedure among experts using baseline clinical information only, excluding any information of emerging biomarkers to prevent underestimating their accuracy.

The reference diagnosis is also determined by a consensus procedure among experts based on clinical information on the course of symptoms over a two-year time period and applying the core clinical criteria for the diagnosis of dementia due to AD [8] and core clinical criteria for the diagnosis of MCI due to AD [7]. Experts are kept blind for any information of the emerging markers under evaluation. Evaluating all cases by expert panel discussion meetings is highly time consuming. Therefore, first expert raters will assess all cases by means of an internet based form and if consensus is not reached the case will be discussed by a panel discussion meeting. The consensus diagnosis during the expert panel meetings is based on a modified Delphi method in which face-to-face discussions are held [45,46].

### Analyses

Several diagnostic procedures based on current practice and emerging biomarker information (index tests) are compared to the reference diagnosis. First, AD aetiology based on the core clinical criteria [7,8] is evaluated. This is reflected by the baseline diagnosis as determined by the consensus procedure. No information of any emerging biomarker is included. Second, AD aetiology based on the research criteria as established by the National institute on aging and the Alzheimer’s Association are evaluated [9]. At last, several explorative decision rules are applied including clinical information and biomarker information to determine AD aetiology and suspected progression of cognitive decline within two years.

#### Research goal 1: Diagnostic test accuracy

Diagnostic test accuracy is determined by relating index test results to the reference diagnosis (reference test). All diagnoses consist of a dichotomous outcome value on underlying pathology of the clinical syndrome and on (expected) progression of cognitive decline within two years. Separately for aetiology and progression of cognitive decline each index test result for each case is indicated as either true positive, true negative, false positive or false negative based on the reference diagnosis (reference test). This enables the calculation of accuracy estimates: sensitivity, specificity, positive predictive value, negative predictive value, likelihood ratio and (an increase of) the Area Under the Curve of a Receiver Operating Characteristic curve.

Finally, novel innovative diagnostic tests are developed during the course of this study by other cooperating researchers for which proof of principle does not yet exist. These tests will be evaluated as soon as evaluation in clinical subjects is possible. To assess diagnostic accuracy the tests will be applied in subgroups of the cohort retrospectively (for CSF samples) or using a case–control design.

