### Subjects

For the study, 241 consecutive patients of the participating memory clinics who were suspected of having a primary neurodegenerative disease were included for participating in the study from October 2009 to May 2011; this included all patients with subjective and/or objective memory complaints. Eligibility criteria were chosen to represent the current clinical situation and enable generalisability to clinical practice (see Table 1). Informed consent was obtained from both the patient and the informal caregiver. Gender, age and reason for refusal were obtained for patients unwilling to participate.

**Table 1 T1:** Eligibility criteria for subject selection

*Inclusion criteria*	
-	All new consecutive patients of the participating memory clinics who are suspected of having a primary neurodegenerative disease
-	Mini-Mental State Examination: ≥ 20
-	Clinical Dementia Rating: 0 – 1
-	Availability of a reliable informer or proxy (who visits or contacts the patient at least once a week)
*Exclusion criteria*	
-	Normal Pressure Hydrocephalus, Huntington’s disease
-	Less than two years ago a transient ischaemic attack (TIA) or cerebral vascular accident (CVA) or TIA/CVA followed (within three months) by cognitive impairment
-	Psychiatric history (schizophrenia, bipolar disorder or psychotic problems (not otherwise specified), less than 12 months ago)
-	Major Depression according to the DSM-IV, less than 12 months ago
-	Cognitive problems due to excessive alcohol use (based on clinical judgement)
-	Brain tumour, epilepsy, encephalitis
-	Probably not available for follow-up

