## Discussion

This research protocol describes the methods used to assess the clinical and economic value of new diagnostic approaches for the diagnosis of AD. A delayed-type cross-sectional accuracy study design is chosen because a randomized clinical trial comes with ethical issues, long follow-up time and limited power. Two hundred forty one consecutive patients suspected of having a primary neurodegenerative disease are followed up for two years and a reference diagnosis is determined by an independent consensus expert panel. Eligibility criteria are chosen to maximally reflect a patient cohort within clinical practice.

Several other multi-centre trials study the relative value of new biomarkers for early evaluation of AD and related disorders. The Alzheimer’s Disease Neuroimaging Initiative (ADNI) in North America is aimed to identify neuroimaging measures and biomarkers associated with cognitive and functional changes in healthy elderly subjects and in subjects who have MCI and AD [51]. Furthermore, the ‘Development of Screening Guidelines and Clinical Criteria for Predementia AD’ (DESCRIPA) study is aimed to develop screening guidelines for predementia AD in the general population [52]. Both include markers in PET, MR imaging and CSF. The uniqueness of this study is the assessment of resource utilization and quality of life to enable an economic evaluation. Furthermore, the decision analytic model enables the evaluation of the optimal diagnostic strategy and the evaluation of diagnostic techniques to be developed during the study in sub-cohorts of the study population. At last, without a disease modifying treatment, the added value of biomarkers is uncertain. Therefore, the availability of such treatment is explored in the sensitivity analysis.

The study has some limitations. It focuses on applying new tests for diagnostic or prognostic goals. Screening and treatment monitoring are outside the scope of this study. A follow-up period of two years was taken as a compromise to maximise the time for the disease to express symptoms of progression (to prevent false negative reference diagnoses) and to minimize the time to prevent the start of a new disease episode after the baseline assessment (to prevent false positive reference diagnosis). It may take up to 10 years before all symptoms of dementia come to expression in subjects with AD pathology [53].

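### For the aetiology endpoint, a correct early amyloid result in a patient still without MCI or dementia at 24 months is scored false positive, and the scoring rule makes no allowance for this

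*Protocol article*

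**What the plan says.** All points are in the protocol article.

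- **Entry.** Table 1 (Subjects) admits "Clinical Dementia Rating: 0 – 1", and the text says that "this included all patients with subjective and/or objective memory complaints".
- **Reference.** Under Study design, "a two-year follow up of the clinical course is used as a proxy to obtain information on the state of the disease at baseline". The section on the baseline and reference diagnosis says that the expert panel works by "applying the core clinical criteria for the diagnosis of dementia due to AD [8] and core clinical criteria for the diagnosis of MCI due to" the same disease, and that it is blind to the emerging markers.
- **Comparator.** The Analyses section bases the baseline clinical diagnosis on the same two sets of core clinical criteria, again without emerging biomarkers.
- **Order of marker change.** Under Emerging biomarker data: "A pathological cascade is hypothesized in which basically Aβ markers become abnormal first, followed by neuronal injury".
- **Scoring.** Research goal 1 gives each diagnosis two yes/no outcomes: the pathology behind the syndrome, and cognitive progression within two years. For each outcome separately, "each index test result for each case is indicated as either true positive, true negative, false positive or false negative based on the reference diagnosis".
- **Use of the labels.** Research goal 2 uses correctness against the reference to define the correctly diagnosed subgroup and the cost per correct diagnosis. Research goal 3 takes accuracy results into the decision model.
- **Disclosure.** The Discussion calls two years a compromise between false negative and false positive reference diagnoses. It adds that the full set of dementia symptoms may take as long as 10 years to appear in people with AD pathology.

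**The concern.** The question for aetiology is whether AD pathology is present at baseline. The reference can answer yes only once that pathology has produced MCI or dementia. For a patient with pathology who has reached neither by 24 months, the reference is negative whatever the truth.

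The error does not fall evenly on the strategies being compared. Amyloid markers are the ones the protocol expects to turn abnormal first, so they are the most likely to be positive in such a patient and to be marked wrong. The baseline clinical diagnosis uses the same criteria as the reference, so it tends to miss the same patient and to be marked right. At stake are the apparent specificity, positive predictive value and accuracy of amyloid markers, and therefore the accuracy gain over current practice and the cost per correct diagnosis.

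The cause is the length of follow-up relative to disease stage. Blinding the panel does not remove it.

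**Working it through.** **The plan's own figure.** The sample size of 219 reproduces as two independent proportions, 80% against 90%, two-sided 5%, with the printed β of 80% read as power. Unpooled variance gives 197 in one group, and 197/0.90 = 219 after 10% drop-out. This does not bear on the point. Only the 10-point relevant difference is used below, as a yardstick.

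**Inputs.** From the document: 241 patients, two-year reference, 10-point difference. Not in the document, and therefore assumed:
- p, the prevalence of AD pathology among CDR 0 patients
- q, the share of those with pathology who reach MCI or dementia due to AD within two years
- s, the share of the cohort at CDR 0

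The marker is taken as error-free for pathology. The reference is taken to make no false positive calls.

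**Formulas within CDR 0.** Reference-positives are pq. Patients with pathology whom the reference calls negative are p(1 − q), and the marker is charged a false positive for each.
- Apparent sensitivity = 1; apparent specificity = (1 − p)/(1 − pq); apparent PPV = q
- Apparent accuracy = 1 − p(1 − q), so the loss is p(1 − q)
- A rule that calls nobody AD has accuracy 1 − pq
- Marker's deficit against that rule = p(1 − 2q)

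| p | q | Specificity | PPV | Marker accuracy | Accuracy of calling nobody AD | Deficit |
|---|---|---|---|---|---|---|
| 0.10 | 0.80 | 0.98 | 0.80 | 0.98 | 0.92 | −0.06 |
| 0.20 | 0.40 | 0.87 | 0.40 | 0.88 | 0.92 | 0.04 |
| 0.30 | 0.20 | 0.745 | 0.20 | 0.76 | 0.94 | 0.18 |
| 0.30 | 0.60 | 0.85 | 0.60 | 0.88 | 0.82 | −0.06 |
| 0.40 | 0.20 | 0.65 | 0.20 | 0.68 | 0.92 | 0.24 |

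The loss p(1 − q) is present for any q below 1. The deficit against calling nobody AD exists only for q below 0.5; above that the marker comes out ahead.

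**Whole cohort.** If everyone outside CDR 0 is scored correctly and all 241 have an amyloid result, the loss is s·p(1 − q):

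| s | p | q | Accuracy loss (points) | Patients scored false positive (of 241) |
|---|---|---|---|---|
| 0.10 | 0.10 | 0.50 | 0.5 | 1.2 |
| 0.20 | 0.20 | 0.50 | 2.0 | 4.8 |
| 0.30 | 0.20 | 0.20 | 4.8 | 11.6 |
| 0.30 | 0.30 | 0.20 | 7.2 | 17.4 |
| 0.40 | 0.30 | 0.20 | 9.6 | 23.1 |

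The count of 241 is an upper bound on those with an amyloid result, since PiB PET is done at one centre only; CSF amyloid is not restricted in that way. The 10-point yardstick is a difference between strategies, and the comparator may be credited for the same patients, so the marker's own loss need not be the whole shift in that contrast.

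**The case against.** **The trade-off is disclosed and reasoned.** The design section explains why biopsy and autopsy are not available, and the Discussion weighs a longer follow-up against new disease episodes. This stands, and choosing two years is not an error. But disclosure does not change the scoring rule, which treats every case alike.

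**A reader might infer that two years can never reveal pathology in CDR 0 patients.** The document does not support that. The reference accepts MCI due to AD, so a CDR 0 patient who declines far enough within two years can be reference-positive. The 10 years is an upper limit for the full picture of dementia, so spreading conversion evenly over a decade to obtain q = 20% is not justified either; 20% appears above only as one end of a range. Nor does the document equate CDR 0 with subjective complaints only; these are separate statements.

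**A reader might infer that a perfect marker must look worse than a rule that never calls AD.** That needs q below 0.5 and concerns overall accuracy only. Research goal 1 also lists sensitivity, specificity, predictive values, likelihood ratio and AUC. At p = 0.30 and q = 0.20 the marker's AUC is (1 + 0.745)/2 = 0.87, against 0.50 for the constant rule. The real comparator is an expert consensus, not a constant. Accuracy does, however, drive the sample size and the cost per correct diagnosis.

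**The target is the pathology behind a syndrome, and some index tests are combined rules.** This narrows the point: a combined rule is penalised only if it calls such a patient AD. It does not remove it, because the Emerging biomarker data section gives each test its own aetiology outcome.

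**The model draws on literature and expert opinion and includes parameter uncertainty.** So it cannot be said that the bias passes unchanged into the QALY result. But no reference error is named among the parameters, and spread around a shifted estimate does not correct the shift.

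**Conclusion.** The point holds for the aetiology endpoint. Patients with AD pathology who have not reached MCI or dementia by 24 months are reference-negative. A correct amyloid positive in them, or a decision rule that calls them AD, is scored as an error, while the baseline clinical diagnosis normally scores as correct. The direction is against amyloid markers and should be strongest at CDR 0. The protocol acknowledges the risk, but the analysis it describes does nothing with it before the labels reach the cost per correct diagnosis and the model.

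The size is not determined by the document. Within CDR 0 an error-free marker loses p(1 − q) of accuracy. Across the cohort this is 0.5 to 9.6 points for s of 10–40%, p of 10–30% and q of 20–50%, all of them assumptions. The effect on the QALY result is less certain than the effect on accuracy.

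The two-year progression endpoint matches its follow-up and is not affected. Nor does the finding support removing CDR 0 patients from the main comparison, which would work against the aim of early diagnosis and the wish to represent clinical practice. This is an inexpensive improvement to reporting and sensitivity analysis, and it does not invalidate the design.

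**What to change.** 1. **Research goal 1.** Keep all patients in the main analysis. In addition, report aetiology accuracy separately for baseline CDR 0, 0.5 and 1, and state that in CDR 0 a positive reference means clinical AD within two years. Table 2 shows that CDR is already collected at baseline.
2. **Research goal 3, sensitivity analysis.** Add the sensitivity of the two-year reference for AD pathology as a parameter, by CDR stage and over a wide range, for example 20–100% in CDR 0. Show its effect on the accuracy gain over current practice and on the cost per correct diagnosis. At 100% in every stage the uncorrected result is recovered.

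Reporting by stage shows where the bias lies but does not remove it, so the second step is needed as well. The cost is small: wider intervals within each CDR stage and one more model parameter, whose range will have to come from literature or expert opinion. No new data collection is required.
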